## Methods

### Design and setting

The trial takes place in six sites from three states of Australia. All sites are public hospitals, with two sites part of a specialist oncology facility. The volume of patients through each centre differs, so sites will not contribute equally to participant recruitment.

Ethical approval has been obtained from the Human Research Ethics Committees of participating states (Peter MacCallum Cancer Centre Ethics Committee, Project No: 09/07; Ethics Review Committee Royal Prince Alfred Zone, Project No: X11-0112 & HREC/11/RPAH/154; Royal Brisbane & Women’s Hospital Human Research Ethics Committee, Ref No: HREC/11/QRBW/202).

This study is a multicentre, prospective, randomised controlled intervention trial for patients receiving radiotherapy for gynaecological cancer, with follow-up of 1 year post-end of treatment.

### Participants

Patients will be consecutively screened for eligibility at participating sites. Inclusion criteria are: (1) have a confirmed diagnosis of gynaecological cancer; (2) be scheduled to receive radiotherapy with curative intent to the pelvis; (3) be aged 18 years or older; and (4) be able to read and write English, and give informed consent. Exclusion criteria are: (1) a severe psychiatric or cognitive disorder; (2) treatment with palliative intent; or (3) previous treatment with radiotherapy to any part of the body.

Patient eligibility will be confirmed by the treating clinician and the trained data manager will provide additional information and gain written informed consent. Prior to radiotherapy commencement, the treating clinician will complete a vaginal examination and document baseline vaginal toxicity. The data manager will be responsible for liaising with the trained nurses and peers to organise and coordinate intervention delivery.

### Intervention

The psychosocial intervention will involve two linked components: (1) nurse-led consultations; and (2) peer telephone support. These elements will be delivered at four critical points in the illness trajectory: pre-treatment, mid-treatment, treatment completion and post-treatment. Figure 
1 provides a schematic diagram of the intervention components.

**Figure 1 F1:**
[figure not shown]
**PeNTAGOn study design: a randomised controlled trial.** Schematic diagram of the PeNTAGOn study design. Patients will be screened for eligibility (criteria listed), then approached and randomised to receive usual care or usual care with the nurse and telephone peer support intervention. Critical intervention time-points are highlighted pre-, mid-, end- and post-treatment. Time-points for follow-up data collection to 12 months post end of radiotherapy are noted. Estimates for sample recruitment and retention are shown in each step of the diagram. Box 1 describes baseline data collected. Box 2 describes key features of the intervention. Boxes 3 to 7 describe follow-up data collection. AQ, Adherence questionnaire; CaTS, Cancer Treatment Survey; FACT-G, Functional Assessment for Cancer Therapy - General; GC, Gynaecological cancer; HADS, Hospital Anxiety and Depression Scale; LENT SOMA, Late Effects of Normal Tissues / Subjective-Objective Management Analytic; MSAS-SF, Memorial Symptom Assessment Scale Short Form; RT, Radiotherapy; SCNS-SF, Supportive Care Needs Survey - Short Form; SVQ, Sexual function-vaginal changes questionnaire.

#### Nurse-led consultations

##### Training

Two specialist cancer nurses will be trained to provide the consultations at each site. The intervention nurse will not be involved in the management of ‘usual care’ patients in order to prevent diffusion of the intervention. Training will comprise online education in distress management, aspects of survivorship and modules on the psychosexual care of women with GC. Training also includes a 2-day workshop facilitated by experts in communication, cancer nursing, patient education and coaching, and psychosexual rehabilitation. The workshop learning objectives are to: (1) gain an understanding of the project including preventing intervention diffusion; (2) develop skills to elicit, explore and respond to patient concerns; and (3) coach and communicate effectively with patients on the use of evidence-based self-care strategies and psychosexual issues. Specific strategies include pelvic floor exercises and the use of vaginal dilators and moisturisers. Training methods included didactic and interactive teaching, rehearsal of skills and constructive feedback using role-plays with actor-patients and the provision of a detailed intervention manual.

##### Intervention session 1: pre-treatment, face-to-face, 1 hour

Patients with cancer often report increased unmet needs related to the worries and fears of family members
[39], so women will be encouraged to bring a significant other to the consultation. Given that anxiety related to treatment is typically highest just prior to starting treatment
[3] and based on Level I evidence on treatment preparation
[12,13] each patient will be given a brief tour of the treatment unit followed by a private consultation. The nurse will first ascertain the patient’s understanding of their situation and clarify misconceptions. A radiotherapy question prompt sheet developed from the literature and with consumer and professional input will be administered by the nurse and at the first three sessions to guide tailoring of the intervention. The patient identifies her top three concerns for focus in the session, with further concerns addressed at future sessions. The prompt sheet also assesses global distress using the Distress Thermometer
[40]. Anxious patients will be trained to use the strategy of controlled breathing with positive self-talk, an effective self-care activity to reduce treatment-related anxiety
[41]. The prompt sheet will aid a discussion of the woman’s supportive care needs and possible MDC referrals. The nurse will discuss vaginal health, psychosexual rehabilitation, and if appropriate, menopause and infertility. Coaching and rehearsal of self-care for side effects and stress-reduction will be offered, and tailored fact-sheets and information provided which can improve recall
[30]. At the end of each session the nurse arranges a time for a call with the peer volunteer. The nurse also confirms any particular concerns the patient does not wish to discuss with her peer.

##### Intervention session 2: mid-treatment, face-to-face, 30 minutes

Since side effects of radiotherapy commonly commence at 2 to 4 weeks into treatment
[17], this session addresses side effects and coaching in self-care strategies. The woman will be provided with lubricants, informed about and shown how to use the dilator and perform pelvic floor exercises. The timing of commencing dilator use will be according to local hospital policy. In addition, the nurse will assess the patient’s experience of treatment, normalise fears and ask about the call with her peer. The nurse will address any ongoing issues from the first session and new concerns and provide coaching in relevant self-care. Barriers to self-care and stress-reduction strategies will be elicited and the importance of adherence reinforced
[42].

##### Intervention session 3: end of treatment, face-to-face, 30 minutes

Some patients report relief upon completing treatment however research by Jefford *et al*. has shown that this is often a time of uncertainty and anxiety
[43]. This may be compounded by treatment side effects, both acute and long-term
[2,5,6,14]. In this session the woman can discuss anxieties related to treatment completion, ongoing issues and treatment side effects with the nurse. Vaginal health and psychosexual recovery will be explored, including the resumption of sexual activity if desired. The nurse will provide the patient with a Survivorship Care Plan (SCP) detailing the woman’s diagnosis and treatment received, planned follow-up schedule, common ongoing or new treatment side effects, and how to manage them. With the patient’s permission, the nurse will fax a copy of the SCP to the patient’s primary care doctor.

##### Intervention session 4: 2 weeks post-treatment, telephone, 30 minutes

Many people report feeling abandoned and isolated after leaving the hospital system and an expectation by family and friends to return to ‘normal’
[43]. The nurse will explore concerns and experiences since completing treatment, address barriers to using self-care strategies and reinforce the importance of vaginal dilator use. The nurse will elicit new or remaining concerns and respond accordingly before prompting for any final questions.

#### Telephone peer support

Each woman will be linked with a peer who will provide four telephone support sessions throughout the treatment course. Peers will be matched to the participant’s medical and personal circumstances such as diagnosis, treatment type, age and area of residence. Approximately 30 peers will be trained over the course of the trial, accounting for peers taking breaks or withdrawing from the study. Each peer will support a maximum of two patients at any one time.

##### Training

Careful selection and training of peers and ongoing professional supervision is critical for the success of peer support programs
[34]. The shortcomings of previous peer support studies, particularly regarding inadequate reporting of peer recruitment, training and support, will be overcome through a rigorous multistage selection and training process, the provision of ongoing training, supervision and debriefing by an experienced cancer nurse, and provision of a detailed intervention manual
[44]. Peers will be past GC patients identified by clinical staff at participating centres and sent an invitation letter about the program. Peers must be over 18 years old, speak English and be at least 2 years post treatment. Those with cancer recurrence or a history of major psychiatric illness are ineligible. Experts in assessing peer volunteers for phone-based cancer peer-support programs will conduct screening phone interviews with interested peers. Suitable women attend a 2-day workshop. The workshop learning objectives are to: (1) gain an understanding of the project including privacy and confidentiality; (2) develop skills in active listening and providing empathy; and (3) reinforce self-care strategies recommended by the nurse. In subsequent weeks, they complete practice calls with an actor-patient to apply these skills, and feedback is provided by a communication skills expert.

##### Peer intervention sessions

The peer will contact the patient 1 week after each nurse consultation except for the last session when the peer calls the patient 4 weeks post treatment. The nurse will call the peer after their consultation with the patient, and send a check-list of the patient’s concerns and the individualised self-care plan. Using a structured format, the peer’s role will be to:

(1) Provide psychosocial support to the patient: Using open questions, empathy and active listening, the peer will establish rapport with the patient, hear her story and experiences and normalize the woman’s emotional reaction.

(2) Encourage adherence to the recommended self-care strategies: The peer will be trained to reinforce information and coaching on basic self-care strategies recommended by the nurse, including problem solving difficulties. For more complex problems or additional needs, the peer will encourage the patient to contact the nurse or access additional sources of information and support, such as the Cancer Council Helpline. If the peer has concerns about the patient, she will contact the nurse and discuss them.

### Sample size

The treatment effect is conservatively estimated to result in group differences of 0.35 standard deviations for continuous outcome measures
[45-47]. With the Hospital Anxiety and Depression Scale total score (HADS-T) as the primary outcome, to achieve ≥80% power at a 5% significance level, the required sample size in each arm is 130 at the 12-month follow-up. With a patient approach rate estimated at 85%, consent rate estimated at 60% and attrition estimated at 15%, 600 participants will need to be approached to achieve a sample of 260.

### Study integrity

The study design and reporting will adhere to the Consolidated Standards of Reporting Trials (CONSORT) statement
[48]. Usual care practice will be monitored yearly with a questionnaire administered to nurses most involved with the usual care of women with GC receiving radiotherapy at each site. A consecutive sample will be randomly allocated at the central site by computer with a weighted-biased coin method 1:1 to either intervention or usual care arms. Participants will be stratified according to treating hospital and treatment type. Minimisation will be used to balance the randomisation across the strata.

Participants will not be informed of their allocation until the baseline questionnaire has been received. Blinding of patients and providers to experimental arm cannot be achieved with this study design, however outcome assessment will be by self-reported questionnaire, thereby obviating the need for researcher blinding. Usual care arm participants will receive a booklet on their specific cancer diagnosis, treatment, and psychosexual recovery to meet minimal ethical standards
[49], and information will be provided as per usual practice by their treatment team. Reasons for attrition will be recorded and recruitment and dropout bias assessed.

All nurse and peer sessions will be audio-taped and a random sample of 15% of sessions will be assessed for adherence to protocol. Length of sessions will be reported. The first five calls or consultations made by each peer and nurse will be reviewed and feedback provided on adherence to protocol, use of communication and coaching skills and areas for improvement.

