**Methods/design:**

This multifaceted intervention comprises four nurse-led consultations coupled with four phone calls from a peer support volunteer (GC survivor). The evidence-based intervention will be delivered at critical points in the illness trajectory: pre-treatment, mid-treatment, treatment completion and post-treatment. Nurses and peers undergo 2-day intensive training workshops, are guided by comprehensive study intervention manuals and receive ongoing supervision and support. Eligible patients will have a diagnosis of GC, be scheduled to receive curative radiotherapy, be aged 18 years or over and speak English. Three-hundred and six participants will be randomized to receive usual care or usual care with the intervention package. Study outcome measures will be collected at baseline, day 1 of radiotherapy and 1, 6 and 12 months post radiotherapy. Clinical assessments of vaginal toxicity will occur at baseline, and 3, 6, and 12 months post radiotherapy.

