#### Secondary endpoints

Compared to the usual care group, the intervention group will report:

1. Lower informational and psychosocial supportive care needs and lower symptom distress from baseline to follow-up at 4 weeks post treatment,

2. Better preparation for treatment from first follow-up immediately prior to the first radiotherapy treatment to follow-up at 4 weeks post treatment,

3. Higher psychosexual functioning from baseline to follow-up at 6 and 12 months post treatment,

4. Higher quality of life from baseline to follow-up at 4 weeks post treatment, and

5. Less vaginal stenosis at 3, 6 and 12 months post treatment.

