### Measures

Patients will complete self-report, pen and paper measures. Clinical vaginal assessments will be completed by the treating clinician. Table 
1 presents when measures will be administered.

**Table 1 T1:** Time-points for collection of patient reported outcomes and clinical outcomes for the PeNTAGOn study

**Time-point**	**Questionnaire**
Baseline & clinical exam I: (pre-treatment)	Demographic and clinical variables, HADS, FACT-G, SCNS-SF34-R, MSAS-SF, SVQ, clinical exam I (LENT SOMA scale)
Follow-up 1: (immediately prior to first radiotherapy)	HADS, CaTS
Follow-up 2: (4 weeks post radiotherapy and post intervention)	HADS, FACT-G, SCNS-SF34-R, MSAS-SF, AQ, CaTS and Patient Care evaluation & Referrals
Clinical exam II (3 months post radiotherapy)	Clinical exam II (LENT SOMA scale)
Follow-up 3 & clinical exam III: (6 months post radiotherapy)	HADS, FACT-G, AQ, SVQ, clinical exam III (LENT SOMA scale)
Follow-up 4 & clinical exam IV: (12 months post radiotherapy)	HADS, FACT-G, AQ, SVQ, clinical exam IV (LENT SOMA scale)

AQ, Adherence questionnaire; CaTS, Cancer Treatment Survey; FACT-G, Functional Assessment for Cancer Therapy - General; HADS, Hospital Anxiety and Depression Scale; LENT SOMA, Late Effects of Normal Tissues / Subjective-Objective Management Analytic; MSAS-SF, Memorial Symptom Assessment Scale Short Form; SCNS-SF34-R, Supportive Care Needs Survey - short form, Revised response format; SVQ, Sexual function-vaginal changes questionnaire.

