#### Clinical examination

The treating clinician will conduct clinical vaginal examinations. The LENT SOMA scale (Late Effects of Normal Tissues / Subjective-Objective Management Analytic), objective criteria for vaginal/sexual dysfunction
[50,51] will be used to measure vaginal changes.

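### The self-report reason given for not blinding researchers is wrong for secondary endpoint 5: vaginal stenosis is scored by the treating clinician, who is not stated to be blinded

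*Protocol article*

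**What the plan says.** In the protocol article, Study integrity first concedes that "Blinding of patients and providers to experimental arm cannot be achieved with this study design", and then says that "outcome assessment will be by self-reported questionnaire, thereby obviating the need for researcher blinding". The second statement is general; no outcome is excepted.

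Four other places describe an outcome that does not fit it:

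- Secondary endpoints, item 5: "Less vaginal stenosis at 3, 6 and 12 months post treatment".
- Measures: "Clinical vaginal assessments will be completed by the treating clinician". This comes straight after the sentence on pen-and-paper self-report, so the article itself separates the two kinds of measurement.
- Clinical examination: "The treating clinician will conduct clinical vaginal examinations". The objective criteria of the LENT SOMA scale "will be used to measure vaginal changes".
- Abstract, Methods/design: "Clinical assessments of vaginal toxicity will occur at baseline, and 3, 6, and 12 months post radiotherapy". Table 1 gives the same four time-points.

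On disclosure, Study integrity says only that "Participants will not be informed of their allocation until the baseline questionnaire has been received". It does not say when, or whether, the examining clinician learns the arm.

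**The concern.** Self-report can justify having no blinded researcher only for outcomes that the patient reports. Stenosis is graded by a clinician, so the argument does not reach it, and the article offers no other protection for this endpoint: no masking step and no independent examiner.

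The intervention coaches women in dilator use and pelvic floor exercises (Training under Nurse-led consultations; Intervention sessions 2 and 4). An examiner who knows the arm therefore has a specific reason to expect a difference in stenosis. Grading an examination involves judgement even with objective criteria. Stenosis is also the only clinician-rated outcome among the listed endpoints. If the sentence stands, the stenosis result could be read as though assessment bias had been dealt with.

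**Working it through.** **Step 1. Is the stated premise true of each endpoint?** Endpoints from Study hypotheses, instruments from Measures and Table 1:

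| Endpoint | Instrument | Scored by | Premise true? |
|---|---|---|---|
| Primary: psychological distress | HADS-T | Patient | Yes |
| Secondary 1: needs, symptom distress | SCNS-SF34-R, MSAS-SF | Patient | Yes |
| Secondary 2: preparation for treatment | CaTS | Patient | Yes |
| Secondary 3: psychosexual functioning | SVQ | Patient | Yes |
| Secondary 4: quality of life | FACT-G | Patient | Yes |
| Secondary 5: vaginal stenosis | LENT SOMA | Treating clinician | **No** |

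The premise fails for one endpoint, and the conclusion drawn from it fails there too.

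**Step 2. Could the examiner know the arm?** No sentence says that clinicians are told. Three things make it plausible:

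- The treating clinician may well be one of the providers who, according to Study integrity, cannot be blinded.
- The intervention nurse does not manage usual-care patients, so contact with that nurse points to the arm. Multidisciplinary referrals and the Survivorship Care Plan may do the same.
- The examinations at 3, 6 and 12 months all come after the woman has been told her allocation, and she may mention it.

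**Step 3. Are the plan's own figures affected?** No.

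- Per-arm size for 0.35 SD, 80% power and two-sided 5% (sidedness is not stated; two-sided reproduces the figure): 129 by the normal formula and 129.1 by the t-test version, against a stated 130. Power at 130 per arm is 80.6%.
- Recruitment: 600 × 0.85 × 0.60 = 306 randomised; 306 × 0.85 = 260.1, matching the planned 260.

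These concern HADS-T and do not depend on how stenosis is scored.

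**Step 4. How much could it matter?** The document gives no stenosis rate and nothing on rating error, so what follows is an illustration and not an estimate. Assumptions, none from the document except the 130 per arm: a binary stenosis outcome, no true effect, a two-sided 5% test, and a recorded intervention-arm rate lowered by *b* through knowledge of the arm. With p₁ = p, p₂ = p − b and p̄ = (p₁ + p₂)/2:

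false-positive rate = Φ[(b − 1.96·SE₀)/SE₁] + Φ[(−b − 1.96·SE₀)/SE₁],

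where SE₀ = √[2p̄(1 − p̄)/130] and SE₁ = √{[p₁(1 − p₁) + p₂(1 − p₂)]/130}.

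| True rate p | b = 0 | b = 0.05 | b = 0.10 |
|---|---|---|---|
| 0.20 | 5.0% | 18.5% | 61.8% |
| 0.30 | 5.0% | 14.7% | 46.1% |
| 0.40 | 5.0% | 13.2% | 39.3% |

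Under these assumptions a modest rating shift would be enough to undermine the comparison. The table does not show that such a shift will occur.

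**The case against.** The best defence is that the sentence is loosely worded and misleads nobody. Measures and Clinical examination say openly who scores the vaginal outcome, and objective criteria are specified. The SVQ adds a patient-reported vaginal-changes scale at 6 and 12 months. The word providers may mean only the nurses and peers who deliver the intervention. The data manager, not the clinician, coordinates delivery, so the examiner may often be unaware of the arm.

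Part of this stands. Objective criteria reduce observer bias, though they do not remove it. The SVQ scale is a partial cross-check, but it covers only sexually active respondents and has no 3-month assessment. None of this makes the stated rationale true for endpoint 5, and an examiner who may happen to be unaware is not a masked examiner.

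A reader might also infer more than the document supports:

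- **That the clinician is known to be unblinded.** This is an inference from the word providers. The supportable wording is that blinding is not stated and knowledge of the arm is plausible.
- **That the article wrongly claims the questionnaires are free of bias.** It speaks only of researcher blinding, and the same sentence admits that patients are not blinded.
- **That every post-treatment score is biased.** The product 3 × 306 = 918 counts planned examinations with no attrition; with 260 women it is 3 × 260 = 780. Neither figure measures bias.
- **That the bias must favour the intervention.** That direction is a reasonable expectation, not something the document establishes.

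**Conclusion.** The point holds for secondary endpoint 5 only. The reason given for dispensing with researcher blinding is contradicted by the article's own description of how stenosis is measured, and no other section repairs it. This is an incorrect statement, not a detail left to a fuller protocol or analysis plan.

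The consequence is that the stenosis comparison at 3, 6 and 12 months is open to observer bias of unknown size. This rests on two readings: that the treating clinician can plausibly learn the arm, and that LENT SOMA grading leaves some room for judgement. HADS-T, the sample size and secondary endpoints 1 to 4 fall outside the point. It should be corrected because it changes what can be concluded from endpoint 5, but it does not threaten the primary analysis.

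**What to change.** 1. In Study integrity, limit the self-report rationale to the questionnaire outcomes, and add that vaginal stenosis is assessed by the treating clinician without assured masking.
2. Keep allocation off the examination form. Where a site can manage it, have the LENT SOMA score entered before study-nurse records are seen.
3. Add one field to the form: did the examiner know the arm at the time of scoring (yes, no, unsure)? Tabulate it by arm and time-point.
4. Report the stenosis result as open-label where masking was absent or failed. Recruitment is already open, so count any examination done before the field existed as masking unknown.
5. Do not state that clinicians are unaware of allocation unless sites can ensure it; a flat statement could be untrue of examinations already done.

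The cost is one form field, a short site instruction and a corrected sentence, with no extra assessor, visit or participant. Masking will be imperfect, holding back nurse records until scoring may not be workable at every treating visit, and the stenosis result may have to be described less favourably.
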